### Secondary Objectives

1. Report the rates of CVD; specifically, the rates of undiagnosed or undertreated CVD.
2. Examine the utility of the primary outcome compared to readmissions, mortality and quality of life.
3. Examine the relationship between changes in cardiac function (in the intervention group) from baseline to 90 days, and (E)COPD severity and comorbid CVD.
4. Assess the feasibility of collecting service-use data for an economic evaluation of the intervention in a future RCT
5. Report differences in health costs and estimated quality adjusted life years (QALY) between the 2 study arms.

## Study Population

Patients hospitalised to Northumbria Specialist Emergency Care Hospital with an exacerbation of spirometry confirmed COPD.

### Inclusion criteria

- Age >35 years
- Current / former smoker & smoking burden >10 pack years
- Clinical diagnosis of COPD, supported by previous obstructive spirometry
- Admission to hospital with the primary cause being an exacerbation of COPD

### Exclusion criteria

- Reason for admission not ECOPD in view of attending clinical team.
- Unable to provide informed consent
- Any non-COPD condition likely to limit survival to less than 12 months
- Contra-indication to cardiac CT
- Pregnancy or breastfeeding

## Target enrolment/sample size:

120

## Anticipated rate of enrolment:

7-8 per month

## Estimated study start date:

First patient first visit: 28th November 2020

## Estimated study completion date:

Last patient last visit: 28th February 2023

## Study Design and Methods

### Methods

A randomised (1:1) pilot study of 120 consecutive consenting patients. The intervention group will undergo a comprehensive cardiac assessment and standardised treatment protocols will be followed to treat identified CVD. Patients will be followed for 12 months to gather outcome data. CVD is defined as hypertension, ischaemic heart disease (IHD), HFPEF, HFREF, atrial or ventricular arrhythmia, moderate-severe valvular heart disease or cor pulmonale.

### Schedule of Activities

All patients will have the following assessments (conducted face to face unless specified):

|                                   | Baseline | 90 (+/- 10) days † | 6 months (+/- 10 days) - telephone | 9 months (+/- 10 days) - telephone | 12 months (+/- 10 days) |
|-----------------------------------|----------|-------------------------------|------------------------------------|------------------------------------|-------------------------|
| Demographics, comorbidity         | X        | X                             |                                    |                                    | X                       |
| Medications                       | X        | X                             | X                                  | X                                  | X                       |
| eMRCD                             | X        | X                             |                                    |                                    | X                       |
| Spirometry & inspiratory capacity | X        | X                             |                                    |                                    |                         |
| NYHA class                        | X        | X                             |                                    |                                    |                         |
| Rockwood clinical frailty scale   | X        |                               |                                    |                                    |                         |
| COPD assessment*                  | X        |                               |                                    |                                    |                         |
| Bedside observations α | X        |                               |                                    |                                    |                         |
| ABG                               | X        |                               |                                    |                                    |                         |

|                                                  |   |   |   |   |   |
|--------------------------------------------------|---|---|---|---|---|
| ECG                                              | X |   |   |   |   |
| Laboratory tests β                    | X |   |   |   |   |
| 4m gait speed                                    | X | X |   |   | X |
| SGRQ-C                                           | X | X |   |   | X |
| EQ-5D-5L                                         | X | X |   |   | X |
| Exacerbation frequency                           | X | X | X | X | X |
| Hospital admissions / ED attendances             |   | X |   |   | X |
| Primary & community NHS care visits π |   | X | X | X | X |
| Mortality                                        |   |   |   |   | X |
| Adverse Cardiovascular Events ‡                  |   | X |   |   | X |

† - at clinical stability, defined as > 6 weeks after completion of primary treatment course for COPD exacerbation; \* - includes; BMI, previous spirometry, previous exacerbation / hospital admission / NIV episodes, α- components of NEWS2 scale; π – health service utilisation form; β – full blood count, urea & electrolytes, liver function tests, glucose, albumin, lactate, CRP; ‡ nonfatal stroke or myocardial infarction, and cardiovascular death

In addition to face to face assessments, all patients will be contacted by telephone at 6 and 9 months to complete an assessment of healthcare resource use. In hospital and at 3, 6 and 9 months following hospital discharge, patients will be provided with a health service utilisation form and asked to use this to record all contact with community NHS services. This data will be reviewed with the patient at the face to face (3 and 12 months) and telephone (6 and 9 months) assessments. Data regarding frequency of COPD exacerbations will be collected at these time points; severe exacerbations (requiring admission) will be captured from health records, moderate exacerbations (requiring treatment with antibiotics and/or steroids) will be self-reported.

Clinical stability is required at the 90-day review for accurate assessment of spirometry and, for those randomised to structured cardiovascular assessment, for echocardiography. The 90-day review appointment will therefore be delayed, if necessary, until participants are in a period of clinical stability, which is defined as more than 4 weeks after completion of a course of steroids and/or antibiotics for a diagnosed COPD exacerbation. The research fellow may clinically assess participants to determine if a COPD exacerbation should be diagnosed if a patient is unwell around the time of review. To avoid excessive delay in cases

of recurrent exacerbation, 90 day review will be conducted after the delay has reached 8 weeks, regardless of the recency of exacerbation.

Those randomised to the structured cardiovascular assessment will also undergo:

|                                                     | Baseline       | 90 days | β – troponin T, NT pro-BNP, fibrinogen, cholesterol profile (admission only), HbA1c (admission only); γ - performed at any point during index hospital admission (or within 7 days of admission); ☉ - performed in patients hypertensive during initial hospital stay, without a prior hypertension diagnosis |
|-----------------------------------------------------|----------------|---------|---------------------------------------------------------------------------------------------------------------------------------------------------------------------------------------------------------------------------------------------------------------------------------------------------------------|
| ECG                                                 | X              | X       |                                                                                                                                                                                                                                                                                                               |
| Echocardiogram                                      | X              | X       |                                                                                                                                                                                                                                                                                                               |
| Laboratory investigations β              | X              | X       |                                                                                                                                                                                                                                                                                                               |
| 24 hour cardiac monitor                             | X              |         |                                                                                                                                                                                                                                                                                                               |
| CT coronary artery calcification score and CT chest | X γ |         |                                                                                                                                                                                                                                                                                                               |
| 24 hour BP monitor ☉                     | X              |         |                                                                                                                                                                                                                                                                                                               |

Echocardiography will be performed by a trained clinician or British Society of Echocardiography (BSE) trained physiologist with oversight by an independent consultant imaging cardiologist. If image quality is insufficient for accurate assessment of ventricular function, contrast echocardiography using SonoVue contrast agent will be performed during inpatient admission.

CT Coronary artery calcification score will be performed according to standard protocol by a trained consultant Cardiologist. Reporting will be performed blinded to the presence of known CVD and knowledge of severity of COPD and ECOPD. Assessment of whether CVD is treated adequately will be made with reference to (inter)national guidance. CT chest will be performed without intravenous contrast according to standard local protocol; emphysema severity and airway wall thickening quantified using commercially available software. Slots for CT scanning for of the study are available at the start of the morning list so it is anticipated that all patients will be able to have a CT scan before being discharged. If this is not possible patients can have their CT scan on an urgent outpatient basis, within 7 days of discharge. This will avoid discharge being delayed for study investigations. If patients have had a CT coronary artery calcium score calculated within 6 months prior to recruitment, this test will not be repeated as the score is unlikely to have changed significantly in this time.

Patients who require 24 hour blood pressure monitoring will either have this test during their inpatient stay or it will be done soon after discharge (a member of the research team will fit the monitor at the patient's place of residence and collect it the following day).

## Economic Evaluation

A prospective economic evaluation will be rehearsed to develop and refine methods for a subsequent definitive trial. The main focus will be on how to accurately identify, quantify and value the additional costs of delivering the intervention and the potential resource implications versus usual care. The costing approach will incorporate an NHS perspective (Secondary, Primary & Community care costs), which will help to detect cost-shifting between NHS care sectors. Resources utilised in the intervention group will be identified in terms of CVD investigations, medications and staff time. Subsequent resource utilisation during follow-up will be captured using a number of NHS databases and a patient resource utilisation pro-forma. In-hospital data including A&E attendances and hospital admissions will be collected through case note review and use of hospital coding services. Primary care attendances including GP visits and Nurse visits will be obtained using a patient resource utilisation pro-forma. This will be assessed retrospectively at the four follow up periods (3, 6, 9 and 12 months). This will facilitate the development of a reliable and valid tool to capture resource use. Data on use of services will be combined with appropriate unit cost to produce a cost per trial participant. These will be sourced from a combination of local costings and national databases [23,24].

## Cardiovascular treatments

For any cardiovascular disease identified, treatment will be initiated by the usual care team in keeping with current local (Northumbria Healthcare NHS Foundation Trust) or (inter)national guidelines. No novel treatment regimens are being examined in this study. Communication with the patient's primary care team will be clear and optimisation of treatment will be performed by the GP, in keeping with (inter)national guidance. In order to facilitate optimum communication between secondary care, primary care and the patient, management summaries (summarising the relevant current guidance reflecting best practice) will be written by the supervisory team with the input of local General Practitioners and an expert patient representative. Treatments given to patients will be recorded at follow up visits as part of the assessment of the rate of undertreated cardiovascular disease (a secondary study outcome). Treatment protocols will be accessible online in primary care and published on the trust website. Treatment of patients in usual care arm will be at the discretion of the treating clinicians.

## Covid19 precautions

All research activity will adhere to the strict Northumbria Healthcare NHS Foundation Trust infection control procedures active at the time. Additionally, patients will be contacted prior to attending hospital to ensure they are not showing symptoms of Covid19 infection. We will reschedule this appointment if patients are symptomatic. Additional procedures to minimise the risk of transmitting Covid19 include: social distancing will be adopted during all face-to face assessments; members of the research team will wear the necessary PPE as advised by Public Health England and the Trust infection control policies during the

assessments and investigations; we will aim to minimise patients' exposure to healthcare professionals during their assessments and aim to limit the waiting times within hospital; and study participants will use a separate entrance to the research and development centre, minimising exposure to healthcare professionals, patients and hospital visitors.

## Study Endpoints

Key outcome measures of interest include readmission and mortality. Our primary outcome measure captures both readmission and death, reflects the number and duration of admissions, and places a higher weighting on mortality (particularly if soon after randomisation). To our knowledge this has not been used in a previous trial involving patients with COPD. Secondary outcomes are included to examine the utility of our novel primary outcome, and to gather important descriptive data to enable powering of the subsequent definitive RCT. Readmission, mortality and length of hospital stay will be collected from hospital health records, using Patient Administration System (PAS).

### Primary

1. The number of days spent alive outside of a hospital environment during 12 months post hospital discharge

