## Lay summary

Chronic obstructive pulmonary disease (COPD) is a common lung disease which can flare up and need admission to hospital. Patients with COPD often have heart disease, which worsens their symptoms and increase the chances of death and hospital admission. In the short period after a flare up of COPD, patients are also at a higher risk of heart attacks and irregular heart rhythms, which cause many of deaths and hospital readmissions experienced. Unfortunately, heart disease is often not recognised or not treated adequately in patients with COPD.

We will test whether carefully finding and treating heart disease in patients admitted to hospital with COPD exacerbation is beneficial. 120 patients will take part in this study. 60 patients will be randomly allocated to 'intervention group' and have detailed tests to identify and then treat heart disease. We will compare their outcomes to 60 patients who do not have this assessment.

In all 120 patients, we will record routine clinical information, simple questionnaires and breathing tests. These tests will be repeated 3 and 12 months later. The 60 patients in the intervention group will have detailed heart tests (blood tests, heart scans, and heart monitors). If we find a heart problem we will start treatment. We will compare the two groups to see if patients in the intervention group spend more time living at home during the year after they start the study.

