We propose a randomised pilot study to investigate the impact of a comprehensive cardiac assessment (and standardised treatment of CVD) on days spent alive outside of hospital during 12 months follow up. This patient centred primary outcome measure captures the number and duration of hospital admissions as well as mortality and, whilst it has been used in cardiovascular studies, [21] it is a novel outcome measure in COPD. Data from this pilot study will hopefully lead to a larger, multicentre randomised controlled trial (not part of this proposal). This would be the first study to our knowledge to investigate the impact of treating CVD on outcome in ECOPD and the first study to use this novel patient outcome.

The aims of this project are congruent with many national priorities and recommendations. *Multimorbidity: a priority for global health research*, a report from The Academy of Medical Sciences (April 2018), listed six research priorities. Our proposal addresses Research Priority 6 which highlights the need for research in to integrated healthcare strategies which "improve clinical outcomes, patient-centred outcomes, and the cost-effectiveness of care". The NHS Outcomes Framework identifies: reducing readmissions within 30 days of hospital discharge (Indicator 3b); and reducing mortality from respiratory disease in under 75s (Indicator 1.2) as key markers of healthcare performance. The NICE Multimorbidity Guideline (NG56) recommends that research in to the holistic assessment of multimorbidity should have clear identification of the target population, careful piloting, well planned interventions, and be directed at outcomes relevant to patients (such as quality of life, hospital admission and mortality); the present proposal meets all of these criteria.

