### Secondary

1. Time to readmission or death following hospital admission for ECOPD
2. All-cause readmission rates at 90 days and 12 months post discharge
3. All-cause mortality rates at 90 days and 12 months post discharge
4. COPD exacerbation rates, from health records and self-reported, at 90 days and 12 months.
5. Rates of adverse cardiovascular events\* at 90 days and 12 months post discharge
6. Rate of new diagnosis of cardiovascular disease at 90 days and 12 months
7. Rate of undertreated cardiovascular disease at baseline, 90 days and 12 months
8. Change in 4 metre gait speed at 90 days and 12 months, compared to baseline
9. Mean change in quality of life measured by St. Georges' Respiratory Questionnaire over 12 months.
10. Health costs and estimated Quality Adjusted Life Years (QALY), measured by health records and patient-completed resource utilisation proforma, at 12 months

In the intervention arm we will also report as secondary outcomes:

11. Changes in right heart function† between baseline and 90 days
12. Relationship between changes in right heart function† and ECOPD severity measured using DECAF score
13. Relationship between changes in right heart function† and comorbid CVD
14. Relationship between right heart function† and COPD severity at baseline.
15. The associations between the primary outcome and right heart function at baselinet.

\* nonfatal stroke or myocardial infarction, and cardiovascular death; † Estimated pulmonary artery systolic pressure (PASP) and tricuspid annular plane systolic excursion (TAPSE) measured by echocardiography.

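### The primary endpoint is counted from hospital discharge, which almost certainly follows randomisation and can depend on the arm, and this conflicts with the protocol's own description of the endpoint

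*Protocol*

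**What the plan says.** The Primary subsection of Study Endpoints sets the outcome as "The number of days spent alive outside of a hospital environment during 12 months post hospital discharge". The paragraph that introduces it says the measure "places a higher weighting on mortality (particularly if soon after randomisation"), which places the origin at randomisation. The Lay summary tells patients that the groups will be compared on whether they "spend more time living at home during the year after they start the study", which is a clock from study entry. The Scientific Rationale speaks of "days spent alive outside of hospital during 12 months follow up" and gives no origin.

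Patients are recruited as inpatients; one inclusion criterion is "Admission to hospital with the primary cause being an exacerbation of COPD". Under Schedule of Activities, only those allocated to structured assessment have the echocardiogram, the extra blood tests, the 24-hour monitor and the CT. CT is to be "performed at any point during index hospital admission (or within 7 days of admission"). Contrast echocardiography, where needed, is done as an inpatient. The heart failure management summary asks for echo early in the admission and goes on to starting drugs. The diabetes summary asks for a repeat HbA1c in hospital and referral to the inpatient diabetes service.

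The Randomisation subsection gives the ratio and the strata but not the moment of randomisation. No section says how a patient who dies before discharge is scored.

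**The concern.** A randomised comparison is protected when each patient's outcome is counted from randomisation, or from an event that allocation cannot affect. Discharge is not such an event here, because the arm-specific tests and some of the treatment come before it. Two things follow from the wording.

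- Time in hospital after randomisation, lengthened or shortened by the work-up, does not enter the primary outcome.
- The deaths closest to randomisation, those during the index stay, are the ones the endpoint is said to weight most. They have no 12-month window in which to be counted.

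This trial is meant to supply the effect on this endpoint for powering a definitive trial (Primary Objective) and to establish a new outcome measure in COPD (Importance to patients and the NHS). It also has an interim analysis after 80 subjects that can extend recruitment (Adaptive design). A badly placed origin would pass into all three.

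**Working it through.** The protocol gives no power, SD, mean, effect size or in-hospital mortality, so there is no figure of its own to reproduce. The check is a comparison of the clocks, followed by sensitivity arithmetic on stated assumptions.

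**1. Order of events.** Entry is as an inpatient. Investigations limited to one arm are carried out during the index admission, so allocation must be known before they start. That randomisation precedes discharge is an inference, but a strong one.

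**2. What the discharge clock ignores.** Take two patients discharged 3 and 10 days after randomisation, with no later event.

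| Clock | Stay 3 days | Stay 10 days | Difference |
|---|---|---|---|
| 12 months from discharge | 365 | 365 | 0 |
| 365 days from randomisation | 365 − 3 = 362 | 365 − 10 = 355 | 7 |

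The discharge window also ends on a different day after randomisation for each of them: 3 + 365 = 368 and 10 + 365 = 375. Among patients who survive the year, each day of arm difference in mean index stay after randomisation is thus an omission of about 1 day. For a patient who is discharged and then dies on a given date within either window, the two clocks give the same score.

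**3. Deaths before discharge.** Let m be the mean score of the patients who are discharged, and k the number of index deaths in an arm of 60 (120 patients, 1:1). If the k patients are left out, the arm mean is m. If they are scored 0, it is m(60 − k)/60. The shift is mk/60. The values of m are assumed.

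| m (assumed) | k = 1 | k = 2 | k = 3 |
|---|---|---|---|
| 280 | 4.7 | 9.3 | 14.0 |
| 340 | 5.7 | 11.3 | 17.0 |

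These are shifts in one arm. Similar numbers of deaths in both arms largely cancel in the difference.

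**4. How often it could arise.** With an assumed in-hospital mortality p after randomisation, the expected number is 120p and the chance of at least one is 1 − (1 − p)^120.

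- p = 1%: 1.2 patients; chance 70%.
- p = 8%: 9.6 patients; chance above 99.9%.

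**5. Scale.** The standard error of the difference is SD × √(2/60). For an assumed SD of 60 it is 11.0 days, and for 120 it is 21.9 days.

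**The case against.** The case on the other side has real strength.

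- **Pre-discharge deaths.** A reader might infer that these patients are dropped. The protocol does not say so. Someone who dies in the index admission has spent no days alive outside hospital, so 0 is a natural score, and an analysis plan that is not shown could fix it. In that case the whole shift in step 3 disappears. What stands is that the stated window does not exist for such a patient, and that index-stay days remain uncounted whatever the analysis plan says.
- **Number of clocks.** A reader might count a third origin in the first secondary outcome, "Time to readmission or death following hospital admission for ECOPD". That phrase may simply describe the population, since a readmission cannot come before discharge; the Hypothesis uses similar words descriptively. It should not be relied on. The Lay summary is a plain-language paraphrase and is weaker evidence than the Study Endpoints paragraph, but both point away from discharge.
- **Delay to discharge.** The sponsor has thought about this. Of the early CT slots and the outpatient option it says: "This will avoid discharge being delayed for study investigations". Blood pressure monitoring may also be done after discharge, and dose optimisation is largely left to primary care. These steps lower the risk. They do not cover inpatient echo, contrast echo, repeat HbA1c or specialist referral. The CT footnote also counts its 7 days from admission while the text counts them from discharge, and the two need to be reconciled.
- **Concealment of a longer stay.** Length of stay is collected from hospital records, so an arm difference could be reported. It would still sit outside the primary endpoint.
- **Proof of bias.** A reader might conclude that the randomised comparison is already broken. Nothing in the documents shows that the arms will differ in index stay or index deaths. The exposure is a matter of design, not a demonstrated bias.

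**Conclusion.** The concern holds as a should-fix. The primary endpoint starts at an event that very probably follows randomisation and that allocation can influence, and the protocol's own account of the endpoint contradicts that start.

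The documents do not determine the size or direction of any bias. On the assumed inputs it is 4.7 to 5.7 days in an arm mean per index death left out (nil if scored 0), plus about 1 day for each day of arm difference in mean index stay. Either may be small beside a standard error of 11 to 22 days.

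The conclusion rests on randomisation preceding discharge, which is inferred. The matter goes beyond a detail that an analysis plan could settle, because the origin is written into the endpoint definition. Imprecision in a pilot also does not excuse it, since the same definition is meant to carry into a larger trial, where sampling error would no longer mask a systematic difference.

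**What to change.** Define the primary outcome as days alive and out of hospital over 365 days from randomisation. Count the rest of the index admission as hospital days, and state that a patient who dies before discharge scores 0. State when randomisation takes place. Bring the Lay summary, Scientific Rationale, Study Endpoints paragraph and Primary subsection into line with this one origin. Use the same origin for time to readmission or death and for the mortality outcomes. Keep the discharge-based count as a secondary analysis.

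The cost is small. Deaths, readmissions and length of stay already come from the Patient Administration System. The only other input is the randomisation date, which the protocol does not list but the randomisation service should hold. Mean days will fall slightly in both arms. Secondary outcomes now worded from discharge (readmission, mortality, cardiovascular events) need matching wording or an explicit statement that they keep the discharge origin. Visit and questionnaire timings need not move.
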